### Power and sample size calculations

Our sample size calculations are based upon our primary aim to improve access to kidney transplant referral and also feasibility and resource availability for intervention activities. To test the primary null hypothesis of no difference in referral proportions between the control and intervention groups, our sample size of 134 dialysis facilities (67 facilities in each arm), with an estimated 46 patients per facility, achieves 80% power to detect a moderate difference of 3.1% to 4.8% in referral proportions between the two groups at 5% significance level. The power calculation assumes a 14% crude referral proportion in the control group based on baseline referral data and an intra-cluster correlation coefficient (ICC) of 0.01 to 0.05, respectively, to account for between-facility variation.

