### Target population, setting, and inclusion/exclusion criteria

Under the direction of Centers for Medicare & Medicaid Services (CMS), 18 regional ESRD Networks are responsible for the quality of care of patients with kidney disease in the US. ESRD Network 6 (GA, NC, and SC) has the largest ESRD patient population among the US ESRD Networks, servicing more than 600 dialysis facilities that treat ~40,000 patients. Approximately 47% of the dialysis facilities in ESRD Network 6 are located in GA, and these facilities treated more than 12,000 dialysis patients in 2012 [47]. The RaDIANT Community Study aims to target 134 outpatient dialysis facilities in GA, representing nearly half (47%) of all GA dialysis facilities.

All dialysis facilities within GA were considered for randomization of the intervention (n = 283). To ensure that each facility had a large enough population to detect a change in the main effect of disparity reduction, facilities with a 2012 population of <25 patients (18-69 years of age) were excluded from the potential pool of facilities (n = 11). The remaining facilities were selected in a step-wise selection process: 1) The presence of a racial disparity in transplant referral (n = 75), or 2) crude annual referral in the lowest 50th percentile (referral <0.06; n = 59) for the state. The presence of a racial disparity was based on a difference of the proportion of AA ESRD patients referred and the proportion of white ESRD patients referred. The remaining facilities selected had a calculated crude referral in the lower 50th percentile. The final pool of 134 facilities were randomized by generating a random number to either the intervention (n = 67) or control (n = 67) group (Figure 1). Dialysis facilities in the intervention group are not blinded to intervention activities; however, facilities selected as controls are blinded. Researchers are not blinded to dialysis facility allocation.

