**Facility Demographic and Clinical Characteristics**				
# Patients per Facility, Mean, SD	46.0 ± 25.7	46.6 ± 25.5	45.4 ± 26.0	0.57
Number of Staff, Mean, SD	10.0 ± 7.4	10.1 ± 6.5	9.8 ± 8.1	0.48
For Profit, %	90.3	88.7	88.3	0.91
Average Age, Mean, SD	61.4 ± 5.9	61.2 ± 5.7	61.6 ± 6.1	0.76
% White	40.9	33.5	46.8	<0.001
% African American	56.5	65.4	49.0	<0.0001
% Uninsured	12.2	11.5	12.6	0.51
% Medicaid Only	9.1	11.0	8.5	0.01
% Unemployed	67.1	70.9	64.1	0.06
Time on Dialysis (Years), Mean, SD	4.9 ± 1.8	5.0 ± 1.21	4.8 ± 1.1	0.32
% Receiving No Access to Pre-ESRD Nephrology Care	27.3	26.0	28.3	0.28
% Not Informed of Transplant Options	2.8	3.1	2.4	0.28
% Diabetes	59.9	59.9	59.0	0.51
% Hypertensive	89.6	91.4	88.1	0.02
% AV Fistula	13.1	13.8	12.3	0.49
% of Incident Patients with AV Fistula	29.7	28.7	30.5	0.46
Average Count of Comorbidities, Mean, SD	3.0 ± 0.8	3.0 ± 0.8	2.9 ± 0.9	0.30
% ESA Prior to Dialysis	17.6	18.0	18.0	0.25
Standardized Mortality Ratio	1.06	1.07	1.05	0.41

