**Transplant Access Measures at Baseline**				
% Waitlisted (Age < 70 yrs only)	17.8	15.5	20.4	<0.0001
Standardized Transplantation Ratio (2008–2011)	0.56	0.46	0.68	<0.001

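### The stated 80% power assumes facilities of equal size; with the size spread in Table 1 it is about 76% (ICC 0.01) and 73% (ICC 0.05) before baseline adjustment

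*Protocol article*

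**What the plan says.** The section on power and sample size states that "our sample size of 134 dialysis facilities (67 facilities in each arm), with an estimated 46 patients per facility, achieves 80% power" and that this is enough "to detect a moderate difference of 3.1% to 4.8% in referral proportions between the two groups", "at 5% significance level". It "assumes a 14% crude referral proportion in the control group based on baseline referral data" and uses an "intra-cluster correlation coefficient (ICC) of 0.01 to 0.05, respectively, to account for between-facility variation". It gives one facility size and no allowance for variation in size.

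Table 1 has a row "Patients per Facility, Mean, SD", which for the 134 randomized facilities reads 46.6 with SD 25.5 (46.0 with SD 25.7 for all 283 Georgia facilities).

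Under Outcome measures, the referral denominator is adult patients under 70. Under Statistical analyses, the primary comparison is an ANCOVA of facility referral rates adjusted for the baseline rate. No weighting by facility size is mentioned.

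**The concern.** When facilities differ in size, a fixed total of patients carries less information than the same total split evenly. An SD more than half the mean is too large to ignore, and it describes the randomized pool itself. A power statement that leaves it out is optimistic on the document's own figures.

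What is at stake is how the result will be read. If the trial finds no difference, readers will use 3.1 to 4.8 points as the range of effects it had a good chance of finding. If the true range is wider, that reading claims too much.

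**Working it through.** **Inputs.** From the power section: 67 facilities per arm, m = 46, control proportion 0.14, ICC 0.01 or 0.05, alpha 5%. From Table 1: CV = 25.5/46.6 = 0.547, so CV² = 0.299. The test is taken as two-sided because a one-sided test does not reproduce the stated figures (it gives 87% and 88%).

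**Step 1: reproduce the plan.** Equal-cluster design effect DE = 1 + (m − 1)·ICC; effective n per arm = 67·46/DE = 3082/DE; two-proportion normal test on that n.
- ICC 0.01: DE = 1 + 45·0.01 = 1.45; n = 2125.5. For 14% against 17.1%, z = (0.031 − 1.96·0.01112)/0.01111 = 0.83, so power is 79.7%.
- ICC 0.05: DE = 1 + 45·0.05 = 3.25; n = 948.3. For 14% against 18.8%, power is 80.6%.

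The differences detectable at 80% are 3.11 and 4.76 points, so the plan's figures are right for equal facilities.

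**Step 2: add the size variation.** DE = 1 + ((1 + CV²)·m − 1)·ICC, with (1 + 0.299)·46 = 59.8.

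| | ICC 0.01 | ICC 0.05 |
|---|---|---|
| DE, equal sizes | 1.45 | 3.25 |
| DE, Table 1 CV | 1.588 | 3.94 |
| Effective n per arm | 1941 | 782 |
| Power at the stated difference | 76.0% | 72.8% |
| Difference detectable at 80% | 3.26 points | 5.27 points |

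**Step 3: dependence on weighting.** The design effect in step 2 applies when facilities are weighted by size. For unweighted facility rates, effective n = 67/[ICC + (1 − ICC)·mean(1/m)]. The documents do not give mean(1/m), so I assumed two size distributions with mean 46.6 and SD 25.5: a lognormal (0.0279) and a shifted gamma with a minimum of 25 (0.0259).
- ICC 0.01: n = 1780 and 1878; power 72% and 75%.
- ICC 0.05: n = 876 and 898; power 77% and 78%.

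With optimal weights power is about 78% and 79% at the two ICCs. All versions fall below 80% before covariate gain, by between about 1 and 8 points.

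**Step 4: baseline adjustment.** Adjusting for a baseline rate with between-year correlation ρ multiplies effective n by 1/(1 − ρ²). Reaching 80% needs an effective n of 2144 (ICC 0.01, 3.1 points) or 933 (ICC 0.05, 4.8 points). From the step 2 values, the ρ required is √(1 − 1941/2144) = 0.31 and √(1 − 782/933) = 0.40. The documents give no ρ.

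If facility effects persist fully from year to year and the remaining variation is independent between years, the largest ρ for unweighted rates is ICC/[ICC + (1 − ICC)·mean(1/m)].
- ICC 0.01: ρ is at most 0.01/0.0376 = 0.27 (lognormal) or 0.01/0.0357 = 0.28 (minimum 25). Reaching 80% from n = 1780 or 1878 would need √(1 − 1780/2144) = 0.41 or √(1 − 1878/2144) = 0.35. The approximation gives 75% and 78% at best; simulating the ANCOVA gives 73% to 77%. Weighted by size, it gives about 79% to 83%.
- ICC 0.05: ρ is at most about 0.65 to 0.67, well above what is needed. The simulated ANCOVA gives 81% to 97% at 4.8 points across the assumed size distributions and correlations.

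**The case against.** The strongest reply is that the plan contains no arithmetic error: its figures follow from its inputs, it calls 46 an estimate, it covers a range of ICCs, and it says feasibility also set the size. That is correct. A reader might infer that 3.1 and 4.8 points fail by the plan's own calculation. They do not: the shortfall appears only once a term for unequal sizes is added.

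A second reply is that the planned analysis adjusts for baseline, a gain the power section does not count, so step 2 alone is too pessimistic. That stands at ICC 0.05. It does not stand at ICC 0.01 for an unweighted facility-level analysis, because with so little between-facility variation the two years' rates can correlate only weakly.

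A reader might go further and infer that 46 is an all-age count, so that the under-70 denominator is smaller and power lower still. Some evidence points that way: the size row has no age limit while another row is marked "Waitlisted (Age < 70 yrs only", and 283 × 46.0 = 13,018 fits the statement that "these facilities treated more than 12,000 dialysis patients in 2012". Other evidence points the opposite way. The Network figures, about 40,000 patients in just over 600 facilities, give about 67 per facility, so 46 could be an age-restricted count. Only 11 of 283 facilities (3.9%) had fewer than 25 patients aged 18 to 69, whereas a mean of 46.0 with SD 25.7 already implies about 18% to 21% below 25 under a lognormal or normal shape. Scaling 46 down to an under-70 share would widen that mismatch. The documents do not settle the question, and they give no under-70 share from which to compute a further loss.

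**Conclusion.** The point holds, with a modest effect. The stated power rests on equal facilities of 46, and Table 1 shows that the randomized facilities are not equal. Before covariate adjustment, power at the stated differences is about 76% and 73% instead of 80%, and the detectable range is about 3.3 to 5.3 points instead of 3.1 to 4.8. This rests on the Table 1 mean and SD applying to the outcome denominator and on size-weighted facilities.

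Under the planned baseline-adjusted ANCOVA, the loss at ICC 0.05 can be recovered. At ICC 0.01 it remains if facilities are unweighted (about 73% to 77% at 3.1 points, on assumed size distributions) and largely disappears if they are weighted by size. The documents therefore do not support calling the trial underpowered across the whole stated range, nor any figure that treats 46 as an all-age count.

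**What to change.** Recompute power from the actual under-70 counts of the 134 facilities. The sponsor should hold these, since facilities were screened on their number of patients aged 18 to 69. Include the variation in size, state whether the ANCOVA weights facilities by size, and restate the detectable range (about 3.3 to 5.3 points before adjustment if the Table 1 figures describe the under-70 population). If the gain from adjusting for the 2013 rate is credited, state the assumed between-year correlation at each ICC. State whether 46 is the under-70 count used in the outcome denominator.

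The cost is one recalculation and a slightly less favourable stated figure at the low-ICC end. No facilities need to be added and the design does not change.

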## Discussion

In this paper, we described the formation of an academic–community partnership; the development of a multicomponent, quality improvement intervention based on results of a community needs assessment; and the selection of dialysis facilities for the RaDIANT Community Study. Few interventions have been conducted to reduce disparities in the early steps of the transplant process [12] and, to our knowledge, no study has described the development of a large-scale, dialysis facility-level, randomized study to improve transplant referral on a state-wide level and to reduce disparities in access to transplantation. This is the first study that we are aware of that collected transplant referral data from collaborating transplant centers on a state level. The detailed description of the development of a multicomponent intervention could help other ESRD Networks, transplant centers, dialysis facilities, or members of the kidney community to develop similar strategies to improve access to transplantation. In addition, other researchers or community members may find that the unique academic, community, and government partnership we utilized in this study protocol may be a feasible way to utilize sustainable interventions within the community to reduce health disparities.

Reasons for racial disparities are multifactorial and may include patient, provider, and system factors [8]. Nearly one-third of ESRD patients are not informed of transplant as a treatment option at the time of ESRD diagnosis [57], and while AA patients comprise a disproportionate part of the ESRD population, AA patients are less likely to be informed about transplantation than white patients [31, 32]. This may be particularly important for our primarily AA ESRD population in the Southeast, where kidney transplant rates are the lowest in the nation [9]. Systemic, coordinated quality improvement initiatives targeting dialysis facilities, including arteriovenous fistula access and influenza vaccination rates [53], have previously resulted in improved access to high-quality care for ESRD patients, and similar interventions may hold promise in reducing disparities in access to kidney transplantation.

Community and academic partnerships can be a useful way to deliver population-based interventions and may have a high potential for reducing health disparities. Targeting ESRD regions in the Southeast, the region with the most racial disparity in transplant access, holds promise for reducing the overall racial disparity in access to kidney transplantation [11]. The RaDIANT Community Study aims to reach more than one-third of the AA ESRD patients in GA within nearly half of dialysis facilities in the state with the lowest kidney transplant rate in the nation. The results of the RaDIANT Community study could help reduce disparities in access to kidney transplantation for AA ESRD patients living in the Southeastern US.

## Abbreviations

AA: African-American
ANCOVA: Analysis of covariance
CBPR: Community-based participatory research
CMS: Centers for Medicare & Medicaid Services
DD: Deceased donor
ESRD: End-stage renal disease
GA: Georgia
GTF: Georgia Transplant Foundation
LD: Living donor
NC: North Carolina
RaDIANT: Reducing Disparities In Access to kidNey Transplantation
SC: South Carolina
SEKTC: Southeastern Kidney Transplant Coalition
STRR: Standardized transplantation referral ratio.
